### Sample size

The stepped wedge design in the schematic (a six-sequence stepped wedge design, with an implementation period and two clusters assigned to the first and last sequences) will give 80% power to detect a change in the proportion of ACS patients in the eight LGAs arriving via ambulance by 11%, from 61% to 72%, with a two-sided significance level of 5%. This detectable difference depends on the number of patients expected to be observed in each cluster (average of 40 patients per LGA in each two-month period; a total of 2240 patients) and on the intra-cluster correlation, estimated to be 0.09 using data from the VEMD (2011-2015). Examination of these aforementioned data indicated that more complex correlation structures, with decaying correlations over time, were not necessary. We used the Stepped Wedge Stata Program for the sample size calculation. No adjustment was made for LGA or participant attrition due to the outcomes being those routinely collected by health services.

## Recruitment

### *Engagement strategies with communities*

Successfully used methods, by the Heart Foundation, will be employed to engage with local communities, including forming local HM Coalitions. Prior to commencement of the study, the CIA, the Project Manager, Partner Investigators and local collaborators (AIs) will set up coalitions in each LGA to engage local stakeholders. We will approach Local Government, community leaders and health service providers (Hospitals, Cardiac Rehabilitation Centres, General Practice Networks, Pharmacies) in each LGA. We will identify possible community groups, local events, promotion opportunities and other opportunities to assist with the intervention delivery. We will advertise HM activities locally (e.g. in newspapers) and on a dedicated HM website.

### Allocation and sequence generation

Over the 16-month study period, the eight LGAs will move into the intervention phase at two month intervals. As four LGAs are in close proximity (Whittlesea-Hume; Greater Bendigo-Campaspe), these LGAs will switch from control to intervention periods at the same time to avoid possible contamination. For planning purposes, allocation and sequence generation has already been performed. Allocation of randomisation was performed blinded, by the CIA, study statistician and overseen by an independent investigator. This was performed by CIA allocating each LGA a study number from 1 to 8, which was then sent to the independent investigator. Following this the study statistician generating the randomisation sequence with the numbers 1 to 8, this information was then linked back to the LGA allocation numbers (Table 4).

*Table 4. Allocation and sequence generation.*

| LGAs        | Time Period |    |    |    |    |    |    |    |
|-------------|-------------|----|----|----|----|----|----|----|
|             | T1          | T2 | T3 | T4 | T5 | T6 | T7 | T8 |
| Bendigo     |             | X  |    |    |    |    |    |    |
| Campaspe    |             | X  |    |    |    |    |    |    |
| Maribyrnong |             |    | X  |    |    |    |    |    |
| Wodonga     |             |    |    | X  |    |    |    |    |
| Warrnambool |             |    |    |    | X  |    |    |    |
| Mildura     |             |    |    |    |    | X  |    |    |
| Whittlesea  |             |    |    |    |    |    | X  |    |
| Hume        |             |    |    |    |    |    | X  |    |

*X = Launch Event*

*T = time period, two months in duration*

*Proposed timeline for intervention. Light grey cells – control period; medium-grey cells- transition period; dark grey cells – intervention period.*

Statistical methods of analyses for the primary and secondary clinical outcomes

Results from the trial will be reported according to the CONSORT extension for stepped wedge cluster randomised designs. LGA and patient demographics will be described by LGA and period. All available primary and secondary outcomes will be analysed at the patient level using mixed-effects logistic regression models with a random intercept for cluster and fixed effects for each period and for the intervention. The Kenward-Roger correction will be applied to adjust for the small number of LGAs. Since there may be imbalance between the LGAs with respect to various baseline characteristics, in a secondary analysis we will adjust for potential confounders known to influence ambulance use that are available in the VEMD (e.g. age, sex, Australian born). Estimated effects will be expressed as odds ratios and as risk differences, with 95% confidence intervals. A secondary analysis will include an interaction between time and treatment to investigate a cumulative effect of the intervention over time. It has been shown that misspecification of the within-cluster correlation structure can lead to confidence intervals of incorrect widths, so sensitivity analyses allowing for more complex within-cluster correlation structures will be considered. Analyses will be conducted in Stata and/or SAS as appropriate.

We will also perform subgroup analyses (e.g. age, sex, country of birth) across the primary and secondary outcomes.

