| The proportion adult members of the community who correctly state they would call an ambulance for two heart attack scenarios. | Heart Watch Survey/Heart Foundation                                                                                                              |
| Rates of Medicare claims for General Practitioner (GP) Heart Health Checks                                                     | Medicare data/Medicare                                                                                                                           |
| Rates of ED presentations that are ACS                                                                                         | VEMD/DHHS                                                                                                                                        |

|                                                              |                                                                     |
|--------------------------------------------------------------|---------------------------------------------------------------------|
| Rates of ED presentations that are unspecified chest pain    | VEMD/DHHS                                                           |
| Proportion of ACS ED presentations via General Practitioners | VEMD/DHHS                                                           |
| Rates of ACS survival                                        | Victorian Admitted Episodes Dataset (VAED)/DHHS                     |
| Rates and incidence of out-of-hospital cardiac arrest        | Victorian Cardiac Arrest registry (VACAR)/Ambulance Victoria        |
| Rates out-of-hospital cardiac arrest survival                | VACAR/Ambulance Victoria                                            |
| Proportion of chest pain (event type 10) calls to ambulance  | Electronic computer-aided dispatch (CAD) records/Ambulance Victoria |
| Proportion of non-chest pain emergency calls to ambulance    | Electronic computer-aided dispatch (CAD) records/Ambulance Victoria |

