The following will be obtained from the Victorian Department of Health's Victorian Admitted Episodes Dataset (VAED):

- Rates of ACS survival (the proportion of ACS patients surviving to hospital discharge to be compared between groups)

The following will be obtained from the Victorian Cardiac Arrest Registry (VACAR):

- Numbers of patients with an out-of-hospital cardiac arrest by LGA and month. Adult population sizes of LGAs will be obtained from the Australian Bureau of Statistics to convert this to a rate for each LGA in each month.[11]
- Survival to hospital discharge following an out-of-hospital cardiac arrest (proportion of patients with out-of-hospital cardiac arrest surviving to hospital discharge out of all patients with out-of-hospital cardiac arrest to be compared between groups[11])

The following will be collected from the Ambulance Victoria computer-aided dispatch (CAD) records:

- Calls to EMS for chest pain (the proportions of chest pain [event type 10] calls to EMS out of all calls to EMS to be compared between groups [12])
- Calls to EMS for non-chest pain (the rate of non-chest pain [non-event type 10] calls to EMS to be compared between groups; adult population sizes of LGAs will be obtained from the Australian Bureau of Statistics to convert this to a rate for each LGA in each month).

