### **3.7.1 Main analysis**

Both a relative risk and an absolute risk difference will be estimated.

The absolute risk difference in arrival at hospital via EMS will be estimated by fitting a mixed-effects regression model with a binomial distribution and an identity link function, and random intercepts for local government areas and fixed effects for each period and for the intervention. The Kenward-Roger correction will be applied to adjust for the small number of local government areas.[16] Results will be presented as a risk difference and 95% confidence interval. In addition, an odds ratio will be estimated by fitting a marginal logistic regression model (including terms for period and the intervention) via generalized estimating equations with an independent working correlation structure with the Kauermann and Carroll correction applied to the standard errors, as recommended by Thompson et al.[17]

In the case of non-convergence of the model with an identity link, estimates will be based on the marginal logistic regression model only.

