### **3.7.2 Different within-cluster correlation structures**

To assess the impact of the assumption of different within-cluster correlation structures on the estimation of the effect of the education campaign on the primary outcome, the analysis estimating a risk difference in Section 3.7.1 will be repeated assuming a block-exchangeable within-cluster correlation structure, including random effects for cluster and cluster-period.

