### **3.8.2 Binary outcomes: whether patient delay time $\leq 60$ mins (in STEMI and suspected STEMI patients); whether prehospital delay time $\leq 120$ mins (in STEMI, ACS, and suspected STEMI patients); survival to hospital discharge (in ACS patients); survival to hospital discharge following an out-of-hospital cardiac arrest; acute coronary syndrome emergency department presentations via General Practitioners; calls to EMS for chest pain.**

These binary outcomes will be analysed according to the approach outlined in Section on 3.7.1. Analysis of the survival to hospital discharge following an out-of-hospital cardiac arrest outcome will only include participants who had an out-of-hospital cardiac arrest.

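### The risk difference for the chest-pain share of EMS calls is modelled without an LGA-by-period variance term, so its interval can be too narrow by an amount the documents do not determine

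*Supplement*

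**What the plan says.** The amended protocol (statistical methods for the primary and secondary clinical outcomes) analyses all available outcomes with "mixed-effects logistic regression models with a random intercept for cluster and fixed effects for each period and for the intervention". Its Table 3 lists "Proportion of chest pain (event type 10) calls to ambulance" as a secondary outcome. The same methods paragraph warns that a misspecified within-cluster correlation gives intervals of the wrong width, and says richer structures will be considered in sensitivity analyses.

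The SAP is more specific. Section 2.5.2 defines the outcome as "the proportions of chest pain [event type 10] calls to EMS out of all calls to EMS to be compared between groups". Section 3.8.2 includes it in its list and states: "These binary outcomes will be analysed according to the approach outlined in Section on 3.7.1". Section 3.7.1 contains two analyses:

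- a risk difference from a binomial identity-link model with "random intercepts for local government areas and fixed effects for each period and for the intervention", using the Kenward-Roger correction;
- an odds ratio from a marginal logistic model fitted by "generalized estimating equations with an independent working correlation structure with the Kauermann and Carroll correction applied to the standard errors".

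If the identity-link model does not converge, only the second is used. Section 3.7.2 adds a cluster-period random effect, but only to assess the impact "on the estimation of the effect of the education campaign on the primary outcome". SAP Table 7 reports it for that outcome alone. SAP Table 5 gives the chest-pain risk difference its own interval, p-value and ICC.

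**The concern.** The model's variance for an LGA-period share comes from binomial sampling plus a constant LGA effect. If the share also moves locally from one period to the next, for reasons not common to all LGAs, the risk-difference model has nowhere to put that movement and counts it as information about the intervention. Kenward-Roger adjusts for estimating the variance components that are in the model. It does not supply a missing one.

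The plan's ground for the simple structure (protocol and SAP sample-size sections) is an examination of 2011-2015 VEMD data on ACS patients, for a design with 40 per LGA-period. The call outcome comes from dispatch records and has all EMS calls as its denominator. Local variation too small to matter in cells of 40 can matter in cells many times larger.

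Raising ambulance calls for chest pain is a stated secondary objective, and the protocol's background discusses the load that non-ACS patients place on emergency services. SAP 3.1.2 makes no multiplicity adjustment, so each reported interval has to stand on its own.

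**Working it through.** **1. The plan's own figure.** Eight LGAs over eight periods, with one transition cell removed per LGA, leave 56 cells; 56 × 40 = 2,240, as stated. Generalised least squares on the 56 cell means, with ICC 0.09 and a difference of 11 points, gives power of 79.4% with variance at 61% and 81.9% with variance at the mean proportion. The stated 80% reproduces, so the design matrix used below is the plan's.

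**2. Why cell size matters.** Let m be calls per cell, p the share and s the SD of the local LGA-by-period movement.

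- Within-cell variance in the model: p(1−p)/m
- True variance: p(1−p)/m + s²
- Ratio: about 1 + m × ρ, where ρ = s²/[p(1−p)]
- False-positive rate at nominal 5%: 2 × [1 − Φ(1.96/√ratio)]

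With p = 0.10 and s = 1 point, ρ = 0.0001/0.09 = 0.0011. The ratio is 1.04 at m = 40, 1.56 at m = 500 and 3.22 at m = 2,000. The sandwich calculation on the 56 cells gives false-positive rates of 5.4%, about 11.5% and about 27%. The same local movement is negligible at the primary outcome's cell size and serious at 2,000.

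**3. Inputs that have to be assumed.** The documents give no call volume, chest-pain share or LGA-period variance for calls. Assumed: a share of 10%; an LGA SD of 1.5 points; 5, 10 or 20 calls per 100 residents a year, applied to the protocol's Table 1 populations (sum 779,316) and divided by 6 for two-month periods. Populations are matched to LGA names by the order of SAP Table 2, and transition periods follow protocol Table 4.

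Smallest LGA at 5 per 100: 33,655 × 0.05/6 = 280 calls. Largest at 20 per 100: 207,058 × 0.20/6 = 6,902 calls. Binomial SDs, √(0.09/m), run from 1.8 points down to 0.36 point. For the primary outcome the SD is √(0.61 × 0.39/40) = 7.7 points.

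**4. False-positive rate of the LGA-intercept-only risk difference** (sandwich variance, unequal cells):

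| Calls per 100 residents a year | Mean m | s = 0.1 pt | s = 0.25 pt | s = 0.5 pt | s = 1.0 pt |
|---|---|---|---|---|---|
| 5 | 812 | 5.1% | 5.7% | 7.9% | 16.3% |
| 10 | 1,624 | 5.2% | 6.5% | 10.9% | 25.7% |
| 20 | 3,247 | 5.5% | 8.0% | 16.7% | 38.3% |

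Binomial simulation with equal cells of 2,000 (4,000 runs per setting) agrees: 5.1%, 6.9%, 11.3% and 27.5% at s = 0, 0.25, 0.5 and 1.0 point.

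**5. Alternatives.** Allowing for LGA-period variation brought the simulated rate to 4.5-5.4% with equal cells, and to 4-7% in a separate simulation with population-scaled cells (500 runs per setting). A linear-scale analogue of the planned GEE with Kauermann-Carroll errors (t, 6 df) gave 5.4-6.9%.

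**The case against.** The strongest reply is that 3.7.1 already contains a robust analysis of this outcome. The GEE's corrected sandwich errors do not depend on the working correlation being right, and the odds ratio has its own interval in SAP Table 5. This stands, and it confines the problem to the risk difference. It does not remove it: the risk difference is reported with its own p-value, the GEE stands alone only on non-convergence, and no rule says which result governs if the two disagree.

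The protocol's promise to consider richer structures is not limited to the primary outcome. That is fair, but it is non-committal, and the SAP carries it out for the primary outcome only. Fixed period effects also absorb movement shared by all LGAs, including the common part of the October-November 2022 flooding, so only differential movement counts.

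A reader might infer more: that any small local fluctuation pushes false positives to 11-40%, or that every LGA contributes thousands of calls per period. The documents support neither. At a local SD of 0.1-0.25 point the rate is 5-8%. At 10 calls per 100 residents a year, the four smallest LGAs would have about 560-910 calls per period. Table 1 counts all residents while SAP 2.5 restricts outcomes to adults, which could lower the counts. In the other direction, the 1.8 million residents stated in SAP 2.2 would make cells about 2.3 times larger (1,800,000/779,316).

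**Conclusion.** The concern holds for one estimate: the chest-pain call risk difference under SAP 3.8.2 and 3.7.1. Its model omits a variance component that the SAP allows for only when examining the primary outcome. The evidence for omitting it comes from a different data source with far smaller cells. The direction is clear: where LGA-specific period variation exists, the interval is too narrow and the p-value too small.

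The size cannot be read from the documents. Under the stated assumptions the false-positive rate runs from close to nominal (5-8%) for local SDs up to 0.25 point, through 8-17% at 0.5 point, to 16-38% at 1.0 point. It is not established that the plan will produce a false positive, nor that the analysis of this outcome as a whole is unprotected. The point is worth acting on because the remedy is already written elsewhere in the SAP.

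**What to change.** In SAP 3.8.2, for calls to EMS for chest pain, estimate the reported risk difference with random effects for LGA and for LGA-by-period (the structure of 3.7.2) and a small-sample t reference. State that this model gives the reported interval and p-value. If it does not converge, rely on the GEE with Kauermann-Carroll errors already planned. State the observed call counts per LGA-period and the estimated LGA-period variance alongside the result.

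The cost is one extra variance term and a few lines of SAP text. In simulation with no local variation at all, the standard error rose from 0.416 to 0.434 point (0.434/0.416 = 1.04, about 4%). Where local variation exists, the interval widens because it should.

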## 2. PROCESS EVALUATION

The process evaluation aims to determine whether program activities have been implemented as intended and to provide details of the intervention of allow their replication. This will use mixed methods including online reports, qualitative interviews, and evaluation surveys and will be reported according the TiDier Checklist.

Process evaluation indicators:

- Participation rates in education and screening: Participation rates in education and screening: HM coordinators will complete an online report for every session – recording number of participants, duration of event, mode of delivery, location, resources used, and content. Heart Foundation will collect website hits and use of online resources (e.g. Heart Age Calculator).
- Lessons learnt: HM coordinators will keep a diary to document barriers and facilitators and we will conduct qualitative interviews with HM coordinators at the end of the study to elucidate key themes.
- Acceptability to individuals: we will conduct brief de-identified session evaluation surveys at the end of every session.
- Reach: ACS patients and Heart Watch participants for the intervention LGAs will be asked if they had participated in any Heart Matter education events, seen and made use of intervention materials.
- Adoption and sustainability by organisations: we will survey partner organisation one year after intervention concludes to see if they have adopted any methods used in this study.

### 3. COST-EFFECTIVENESS EVALUATION

The economic evaluation is conducted as a sub-study to the step wedge cluster randomised controlled trial. The perspective of the economic evaluation is the health care sector and the reference year for costs will be 2022.

A cost consequences analysis and a simulated cost-effectiveness analysis will be undertaken for the economic evaluation of the Heart Matters campaign.

The economic evaluation will be written up based on the consolidated health economics reporting standards and any relevant checklists for reporting economic evaluations of trials using a randomised cluster stepped wedge design. For example, Lung and colleagues have recommended that researchers account for the following in their statistical analyses: correlation between costs and outcomes (individually and within clusters) and in the estimation of incremental cost-effectiveness, the need to make appropriate assumptions about the distribution of outcomes and costs, and adjusting for time-effects (including interactions with intervention effectiveness). These steps are necessary since accounting for secular and within-cluster trends is an additional complexity that needs to be properly accounted for in a stepped-wedged design.

#### **Costs:**

The costs of providing the program (HM coordinators, education packages) will be described. Health sector costs estimated will include those related to the use of ambulances, hospital emergency presentations and admissions as well as the Medicare rebates for Heart Health Checks. Cost-offsets are the costs of disability, deaths or future events avoided and will be estimated based on published cost-of-illness studies or best available evidence that is relevant to the Victorian context.

Costs will be adjusted to the same reference year because of the 16-month study period.

#### **Cost consequences analysis:**

Cost consequences analysis will be used to describe the expected costs and benefits from the Heart Matters campaign, including community cardiovascular risk assessments, survival, out-of-hospital cardiac arrest incidence, and cost offsets.

The steering committee for the Heart Matters campaign will be asked to define the most relevant clinical, process and economic outcomes to be reported in the cost consequences analysis.

A cost consequences analysis is preferred given the nature of the intervention and the type of data being used to determine the primary and secondary clinical and process outcomes. In this type of economic analysis all the relevant health and non-health effects across different sectors can be reported. This is useful when different outcomes cannot be incorporated into an index measure and there are several important outcomes of relevance to decision-makers enabling these to be assessed transparently against the costs of an intervention.

